## Abstract

**Background:**

Many Australian children are insufficiently active to accrue health benefits and physical activity (PA) levels are consistently lower among youth of low socio-economic position. PA levels decline dramatically during adolescence and evidence suggests that competency in a range of fundamental movement skills (FMS) may serve as a protective factor against this trend.

**Methods/design:**

The Supporting Children’s Outcomes Using Rewards Exercise and Skills (SCORES) intervention is a multi-component PA and FMS intervention for primary schools in low-income communities, which will be evaluated using a group randomized controlled trial. The socio-ecological model provided a framework for the 12-month intervention, which includes the following components: teacher professional learning, student leadership workshops (including leadership accreditation and rewards, e.g., stickers, water bottles), PA policy review, PA equipment packs, parental engagement via newsletters, FMS homework and a parent evening, and community partnerships with local sporting organizations. Outcomes will be assessed at baseline, 6- and 12-months. The primary outcomes are PA (accelerometers), FMS (Test of Gross Motor Development II) and cardiorespiratory fitness (multi-stage fitness test). Secondary outcomes include body mass index [using weight (kg)/height (m^2^)], perceived competence, physical self-esteem, and resilience. Individual and environmental mediators of behavior change (e.g. social support and enjoyment) will also be assessed. The System for Observing Fitness Instruction Time will be used to assess the impact of the intervention on PA within physical education lessons. Statistical analyses will follow intention-to-treat principles and hypothesized mediators of PA behavior change will be explored.

**Discussion:**

SCORES is an innovative primary school-based PA and FMS intervention designed to support students attending schools in low-income communities to be more skilled and active. The findings from the study may be used to guide teacher pre-service education, professional learning and school policy in primary schools.

**Trial registration:**

Australian New Zealand Clinical Trials Registry No: ACTRN12611001080910

## Background

Participation in physical activity (PA) is essential for optimizing children’s physical, social, cognitive and psychological development [1,2]. Activity of vigorous intensity may have additional benefits for young people, as physical fitness is a better predictor of metabolic health than total PA [3-5]. Unfortunately lack of PA among children and adolescents is a global concern [6] and current estimates suggest that only 50% of Australian primary school-aged children are meeting the current PA guidelines (i.e., 60 minutes/day of moderate-to-vigorous PA) [7]. In particular, promoting PA among youth from disadvantaged backgrounds is a public health priority because these individuals have reduced access to PA facilities and resources [8,9] and are often less active than those of middle and high socio-economic position [10-12].

The school setting is an ideal environment for the promotion of PA among youth as schools have the necessary equipment, personnel, facilities and curriculum to promote and provide opportunities for PA [13,14]. Numerous school-based PA interventions have been evaluated [15,16], including those specifically targeting youth from low-income backgrounds [17,18]. Multi-component school-based interventions that involve parents and encourage PA within and beyond the school day, are more efficacious than curriculum only interventions [15,16]. Although the evidence for effective school-based interventions is strong, studies rarely report their effect on movement skill competency. This is a notable omission because PA levels decline dramatically during adolescence [19,20] and evidence suggests that failure to attain competency may contribute to this decline, whereas competency may serve as a protective factor against this trend [21,22].

Proficiency in a range of fundamental movement skills (FMS) is considered to be the foundation for an active lifestyle [23] and the primary school years represent the “golden years” of motor skill development [23,24]. FMS include locomotor (e.g., running and hopping), object control (e.g., catching and throwing) and stability (e.g., balancing and twisting) skills [23]. These skills are ideally developed in childhood and subsequently refined into context- and sport-specific skills [24-26]. A recent systematic review of the health benefits associated with FMS competency found strong evidence for a positive association between FMS competency and PA in children and an inverse relationship between skill level and weight status [27]. Teaching movement skills improves both actual and perceived competence [28,29], both of which are important for future PA [30,31]. Indeed, lack of confidence in the physical domain is a major barrier to PA among many children and adolescents [32-34]. Alarmingly, many children finish primary school without achieving mastery in a range of FMS and those from disadvantaged backgrounds often demonstrate the lowest competency levels [11,35].

The low PA and poor FMS competency observed among children living in low-income communities can be explained by socio-environmental factors (e.g., working parents, lack of PA opportunities and unsafe neighborhoods etc.) [36,37], but may also reflect a failure of current school-based programs and strategies [38]. Indeed, the recent Crawford report highlighted both the central role that schools play in the promotion of PA and the dire state of PE and school sport in Australian primary schools [38]. Formative research conducted by Morgan and colleagues indicated that the crowded school curriculum along with inadequate teacher training programs contributes to teachers’ reluctance to teach PE and the poor quality of existing PE programs [39,40]. Combined, these findings illustrate the importance of designing and evaluating school-based approaches to PA promotion among the most vulnerable individuals (i.e., those living in low-income communities). This paper provides the rationale and methods for the Supporting Children’s Outcomes Using Rewards Exercise and Skills (SCORES) intervention. SCORES is a multi-component school-based intervention that combines a range of evidence-based behavior change strategies to promote PA and FMS competency among primary school aged children from low-income communities.

## Methods/design

### Study design

The SCORES intervention will be evaluated using a group randomized controlled trial (Figure 1). The 12-month multi-component PA and FMS intervention will target children in grades 3 and 4 (ages 7 to 10 grades) in eight primary schools. Assessments were conducted at baseline [February–March (Term 1) 2012], and will be repeated mid-program [August–September (Term 3) 2012] and at 12-months post baseline [February–March (Term 1) 2013]. The design, conduct and reporting of this group RCT will adhere to the Consolidated Standards of Reporting Trials (CONSORT) guidelines for group trials [41]. Ethics approval for this study was obtained from the Human Research Ethics Committees of the University of Newcastle, Australia and the New South Wales (NSW) Department of Education and Communities. School Principals, teachers, parents and study participants provided written informed consent. 

**Figure 1 F1:**
[figure not shown]
Study design and flow.

### Setting and participants

The Socio-Economic Indexes for Areas (SEIFA) index of relative socioeconomic disadvantage was used to identify eligible primary schools. The SEIFA index (scale 1 = *lowest* to 10 = *highest*) summarizes the characteristics of people and households within an area and was developed using the following data: employment, education, financial well-being, housing stress, overcrowding, home ownership, family support, family breakdown, family type, lack of wealth (no car or telephone), low income, Indigenous status and foreign birth. Sixteen government primary schools located within 30 minutes drive from the University of Newcastle, with a SEIFA index of ≤ 5 (lowest 50%) were invited to participate in the study and eight schools consented to participate (50% consent rate). All students in grades 3 and 4 (Stage 2) at the study schools were invited to participate in the program. From the 592 eligible children at the eight schools, 460 children consented to participate (78% consent rate).

### Sample size calculation

Power calculations were conducted to determine the sample size required to detect changes in the three primary outcomes [i.e., PA, cardiorespiratory fitness (CRF) and FMS] at the 12-month assessments. All calculations assumed baseline-posttest correlation scores of 0.80 and were based on 80% power with alpha levels set at *p* < 0.05. Using the standard deviation (SD = 33) and intraclass correlation coefficient (ICC = 0.05) values from the Kinder-Sportstudie (KISS) [42], it was calculated that a study sample of N = 440, with 8 clusters (i.e. schools) of 55 students would provide adequate power to detect an achievable between group difference of 11 moderate-to-vigorous physical activity (MVPA) minutes/day [42]. Based on data from the Action Schools BC! (SD = 13) [43] and the KISS (ICC = 0.03) [42] studies, a sample of 440 would also provide adequate power to detect a between group difference of 4 laps on the multi-stage fitness test (i.e., CFR outcome). In the absence of existing ICC values for FMS outcomes, an ICC estimate of 0.05 and a SD of 15 units [44] indicated that the study would be adequately powered to detect a between group difference of 5 units on the TGMD-II gross motor quotient.

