### Blinding and randomization

Baseline assessments were conducted prior to randomization by trained research assistants. The intervention will be evaluated using a group RCT-design and schools were randomly allocated to the control or intervention groups for the duration of the study. Schools were match-paired based on their size and SEP (based on post-code of school) then randomly allocated to the intervention or control group using a computer-based random number producing algorithm by a researcher not involved in the current study. This method ensured that schools had an equal chance of allocation to each group.

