### Statistical methods

The study will be adequately powered to detect clinically important changes in the three primary outcomes at the 12-month assessments. Statistical analyses of the primary and secondary outcomes will be conducted using linear mixed models with PROC MIXED in SAS V 9.1 (SAS Institute Inc, Cary, NC) and alpha levels will be set at *p* < 0.05. The mixed models will be specified to adjust for the clustered nature of the data and will follow the intention to treat principle. Potential moderators of the intervention effects (e.g., ethnicity, socio-economic status and type of school) will be explored using linear mixed models. Differences between participants in the intervention and groups at baseline and differences between completers and those who drop out of the study will be examined using Chi square and independent samples t-tests in PASW Statistics 17 (SPSS Inc. Chicago, IL) software. Hypothesized mediators of PA behavior change will be examined using multilevel linear analysis and a product-of-coefficients test that is appropriate for cluster randomized controlled trials [73].

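### The stated 80% power leaves out school-level degrees of freedom: on 6 df it is about 67–71.5% for MVPA and FMS, and 75–79% for fitness

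*Protocol article*

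**What the plan says.** The Sample size calculation section sets common terms for all three primary outcomes: "All calculations assumed baseline-posttest correlation scores of 0.80 and were based on 80% power", at alpha 0.05. For MVPA it continues "Using the standard deviation (SD = 33) and intraclass correlation coefficient (ICC = 0.05) values" from an earlier school trial, and concludes that a sample of 440 children "with 8 clusters (i.e. schools) of 55 students would provide adequate power to detect an achievable between group difference of 11" min/day. The same 440 children are said to be enough for 4 laps on the multi-stage fitness test (SD 13, ICC 0.03) and for 5 units on the TGMD-II gross motor quotient (SD 15, ICC 0.05).

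The Statistical methods section repeats the claim without qualification: "The study will be adequately powered to detect clinically important changes in the three primary outcomes at the 12-month assessments". It plans linear mixed models that adjust for clustering.

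The Blinding and randomization section gives the unit of allocation: "Schools were match-paired based on their size and SEP (based on post-code of school) then randomly allocated to the intervention or control group". Eight schools therefore means four per arm.

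The article does not mention degrees of freedom, a small-cluster allowance or the sidedness of the test. It does not say whether the 0.80 correlation entered through change scores or through baseline adjustment.

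**The concern.** A design effect inflates the variance to allow for clustering, but it does not allow for that variance being estimated from few clusters. With eight randomized schools, the between-school variation that forms the error term for the group effect has 8 − 2 = 6 degrees of freedom. The two-sided 5% critical value is then 2.45 instead of 1.96, which is too large a difference to ignore. In a simulated school-level comparison with four schools per arm and no true effect, judging the test statistic against 1.96 rejected 9.7% of the time. A test that holds the stated 5% level needs the larger critical value and pays for it in power.

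What is at stake is how far a reader can rely on the stated sensitivity of the trial. If the true effect on MVPA or FMS equals the planned difference, the chance of missing it is about 28.5% to 33%, against the 20% that the article implies.

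**Working it through.** **Inputs**, all from the Sample size calculation section: SD 33, 13 and 15; ICC 0.05, 0.03 and 0.05; differences 11 min/day, 4 laps and 5 units; r = 0.80; 8 schools of 55, so 220 children per arm; alpha 0.05. A two-sided test is assumed, because sidedness is not stated.

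**Standard error of the group difference.**

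SE = √(2 × SD² × f × DE / 220), with DE = 1 + (55 − 1) × ICC.

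The factor f depends on how the correlation is used:
- change score: f = 2(1 − 0.80) = 0.40
- baseline as covariate: f = 1 − 0.80² = 0.36

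Design effects: 1 + 54 × 0.05 = 3.70 for MVPA and FMS; 1 + 54 × 0.03 = 2.62 for laps.

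Worked case, MVPA with change scores: SE = √(2 × 1089 × 0.40 × 3.70 / 220) = 3.83, and 11 / 3.83 = 2.87.

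**Step 1: reproduce the plan's figure.** Normal test, critical value 1.96:

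| Outcome | f | SE | Difference / SE | Power, normal test |
|---|---|---|---|---|
| MVPA, 11 min/day | 0.40 | 3.83 | 2.87 | 82.0% |
| Laps, 4 | 0.40 | 1.27 | 3.15 | 88.3% |
| FMS, 5 units | 0.40 | 1.74 | 2.87 | 82.0% |
| MVPA | 0.36 | 3.63 | 3.03 | 85.8% |
| Laps | 0.36 | 1.20 | 3.32 | 91.4% |
| FMS | 0.36 | 1.65 | 3.03 | 85.8% |

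The change-score version comes closest to the stated 80%. A t test on child-level degrees of freedom (440 − 2 = 438) gives practically the same change-score figures: 81.8%, 88.2% and 81.8%. If the correlation is not used at all, power is only 44%, 51% and 44%, so it was clearly used in some form.

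**Step 2: same inputs and SEs, school-level degrees of freedom.** Noncentral t on 6 df, two-sided, critical value 2.447. The detectable difference is 3.367 × SE, where 3.367 is the noncentrality that gives 80% power on 6 df.

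| Outcome | Power, change score | Power, covariate | Detectable at 80%, change score | Detectable at 80%, covariate | Stated |
|---|---|---|---|---|---|
| MVPA (min/day) | 67.0% | 71.5% | 12.9 | 12.2 | 11 |
| Laps | 74.8% | 79.0% | 4.3 | 4.05 | 4 |
| FMS (units) | 67.0% | 71.5% | 5.9 | 5.6 | 5 |

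**Checks.** A simulated school-level t test for MVPA with change-score variance gave 67.3%, against 67.0% from the formula. Using the 460 children who consented (57.5 per school) instead of 440 moves the change-score powers only to 67.5%, 75.4% and 67.5%. With eight schools and change-score variance, power for MVPA and FMS stays below 79.2% however many children are measured per school.

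**The case against.** Several points on the other side are fair.

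- *The use of the correlation is unknown.* Baseline as covariate is at least as compatible with the planned mixed models as change scores, and it is kinder to the plan. This stands, so both sets of figures are given. Neither brings MVPA or FMS to 80%.
- *Fitness is hardly short.* With baseline as covariate its power is 79.0%, and 80% power applies to 4.05 laps against the stated 4. This stands: the case for laps is borderline.
- *Sidedness is not stated.* A one-sided 0.05 test on 6 df with change-score variance would give about 81%, 87% and 81%. But the article does not state a one-sided test, and two-sided is the usual reading of an unqualified alpha.
- *The ICC may shrink after baseline adjustment.* That is possible, but the article gives one ICC per outcome and no adjusted value. The check uses the stated values.
- *Recruitment and baseline are complete.* This limits what can change, but not whether the stated power is right.

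A reader might also infer more than the documents support. If the four matched pairs entered the model, about 3 df would remain, and with no precision gained from matching the change-score powers would be 50%, 57% and 50%. The article describes pairing for allocation only, does not put pairs in the model, and gives no figure for the variance that matching removes, so those figures are not a property of the plan. A lower correlation than 0.80 would also reduce power, but the article assumes 0.80 and offers no other value. Nor does it say how a non-significant result would be interpreted, so a misreading of such a result cannot be charged to the plan.

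**Conclusion.** The stated power is not what the stated inputs give for a two-sided 5% test in a trial of eight randomized schools. On 6 df it is 67.0% to 71.5% for 11 min/day of MVPA and for 5 TGMD-II units, a shortfall of 8.5 to 13 percentage points against 80%. For 4 laps it is 74.8% to 79.0%, which is borderline. The lower figure in each range is for change scores and the upper for baseline as covariate.

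The conclusion rests on the article's own SDs, ICCs and correlation, equal schools of 55, no dropout, a two-sided test, and the stated ICC applying to the change or adjusted outcome. Six is the most degrees of freedom that an unpaired comparison of eight schools allows. The finding does not show that the design or the planned analysis is invalid. It shows that the claim of adequate power is too favourable for two of the three primary outcomes.

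**What to change.** In the Sample size calculation section, restate power using a two-sided t distribution with school-level degrees of freedom, and say which use of the 0.80 correlation applies. One of these two statements would serve:

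- *Baseline as covariate:* with eight schools (6 df), power is about 71.5%, 79% and 71.5% for 11 min/day, 4 laps and 5 units; 80% power applies to about 12.2 min/day, 4.05 laps and 5.6 units.
- *Change scores:* with eight schools (6 df), power is about 67%, 75% and 67% for the same differences; 80% power applies to about 12.9 min/day, 4.3 laps and 5.9 units.

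In the Statistical methods section, replace the unqualified claim of adequate power with a reference to these figures. Add one sentence noting that entering the matched pairs in the model would leave about 3 df and could lower power further, depending on how much between-school variance the matching removes.

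The cost is wording, and stated figures that look less favourable. No extra schools or children are needed and nothing in the conduct of the trial changes.

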### Blinding and randomization

Baseline assessments were conducted prior to randomization by trained research assistants. The intervention will be evaluated using a group RCT-design and schools were randomly allocated to the control or intervention groups for the duration of the study. Schools were match-paired based on their size and SEP (based on post-code of school) then randomly allocated to the intervention or control group using a computer-based random number producing algorithm by a researcher not involved in the current study. This method ensured that schools had an equal chance of allocation to each group.

### Intervention

SCORES is a 12-month multi-component PA and FMS intervention for primary schools in low-income communities (Figure 2). The socio-ecological model [45] provided a framework for the intervention components. Within this framework, behavior change strategies were guided by Self-Determination Theory (SDT) [46,47] and Competence Motivation Theory (CMT) [48,49]. SDT proposes that social-contextual factors (e.g., motivational strategies used by teachers and parents) can influence individuals’ motivation and subsequent behavior by satisfying three basic psychological needs: 1) *Autonomy*, the need to experience one’s behavior as self-endorsed or volitional; 2) *Competence,* the need to effectively interact with one’s environment and achieve positive outcomes; and 3) *Relatedness,* the need to feel supported and connected with others [46,47]. SDT has been used extensively with adolescents in PE-based research [50-53] and evidence suggests that students who feel self-determined are more engaged and more active in PE lessons [51,52]. In the context of PA promotion, CMT provides a theoretical link between FMS competence and PA [48]. While CMT includes competence and a construct similar to SDT’s relatedness (social support), it differs in its focus on enjoyment and includes global self-esteem as a predictor of behavior. Our integrated model proposes that children who have high levels of perceived and actual athletic competence, receive social support from significant others and feel a sense of control over their PA experiences will enjoy PA and seek opportunities to be active in the future. 

**Figure 2 F2:**
[figure not shown]
SCORES intervention components, potential mediators and outcomes.

The SCORES intervention will be implemented in three phases. Phase 1 will focus on teacher professional learning, student workshops, provision of equipment and the establishment of a school committee. In Phase 2, the research team will work with the school committees to advocate for relevant policy change to promote PA and FMS. In addition, the research team will employ a range of strategies to engage parents and encourage them to support their children’s PA. Phase 3 will address strategies to improve school-community links (e.g., inviting local sporting organizations to assist with school sport programs). The focus of this phase will be program consolidation and the research team will work with schools to establish sustainability. The intervention components are detailed in Table 1 and a description of how the socio-ecological framed intervention will facilitate behavior change at the individual, interpersonal, organizational and community levels is provided below:

*Individual:* While the intervention will involve a number of indirect strategies to support and improve children’s PA behaviors (i.e., through teachers, parents and the community), students will be directly involved in the SCORES leadership workshops which will be delivered by the research team. The workshops will focus on developing leadership and organizational skills necessary for running lunch and recess PA sessions and assisting classroom teachers to deliver high quality PE lessons. These sessions will be designed to satisfy students’ basic psychological needs (i.e., autonomy, competence and relatedness). and enable them to achieve SCORES leadership accreditation.

*Interpersonal:* The SCORES intervention will target teachers, parents and the students themselves as facilitators of behavior change. The teacher professional learning workshops will provide opportunities for non-specialist PE (i.e., classroom teachers) to improve their teaching skills and knowledge in regards to PA promotion and FMS development. The workshops were guided by SDT and CMT and will be used to reinforce the SAAFE (Supportive, Active, Autonomous, Fair and Enjoyable) teaching principles, which were developed for the study and are described in Table 2.

**Table 1 T1:** Intervention components, behavior change techniques and targeted constructs in the SCORES intervention

**Intervention component**	**Dose**	**Description**	**Behavior change strategies**	**Targeted constructs**
1) Student leadership	1 x 2 hours	Students will be provided with an opportunity to achieve SCORES leadership accreditation. Students will attend the SCORES leadership workshop, which will be delivered at the study schools during PE/sport by the research team. This will provide students with formal acknowledgment (i.e. certificates) and rewards (i.e. water bottles, stickers) for their participation. SCORES leaders will be encouraged to set up (i.e. equipment monitor), run (i.e. deliver lunch and recess activities) and promote (i.e. speak on assembly) PA and FMS development in the school setting. Students who complete these tasks will have the opportunity to achieve a yellow award (complete 5 tasks), red award (complete 10 tasks), and blue award (complete 15 tasks), and receive the associated rewards (i.e. certificates, wrist bands, hats, sporting equipment).	▪Provide instruction	▪Actual competence
			▪Model or demonstrate the behavior	▪Perceived competence
			▪Provide contingent rewards	▪Social support
			▪Prompt identification as a role model	▪Enjoyment
			▪Plan social support or social change	
			▪Set graded tasks	
2) Professional learning workshops for teachers	1 x full day for Stage 2 teachers^1^	The research team will deliver professional development workshops for teachers. Workshops will focus on effective teaching methods for the development of FMS, strategies for teaching and assessing FMS, increasing MVPA and enjoyment in PE and school sport (based on the SAAFE teaching principles).	▪Provide instruction	▪Social support
			▪Model or demonstrate the behavior	
			▪Time management	
			▪Provide feedback on performance	
	1 x half day for all teachers at intervention schools	*i) Stage 2 teachers’ workshop:* will be held at the university. This workshop will be provided for Stage 2 teachers only.		
		*ii) Whole-school workshops:* will be delivered in the study schools during one of their scheduled professional learning days.		
3) Parental engagement	4 x newsletters	*i) Newsletters -* Parents of study participants will be provided with newsletters to educate and encourage them to support their children’s PA behaviors. Newsletters will also provide updates and feedback on the project.	▪Provide information on consequences	▪Social support
			▪Provide feedback on performance	
			▪Plan social support or social change	
			▪Provide general encouragement	
	1 x Parent evening	*ii) FMS Homework* – Students will be encouraged to complete practical homework tasks focused on FMS development with their parents/guardians.		
	Weekly FMS homework	*iii) Parent evening –* Parents will be invited to attend an interactive information session on how to promote and increase PA and FMS in the home setting.		
4) Policy and environment	On-going	*i) School committee and policy review and recommendations:* The research team will conduct a review of PA policy in the schools. The research team will work with Principals and school committees to revise policy to support the PA promotion. Policy recommendations include:	▪Provide opportunities for behavior	▪Physical environment
			▪Provide access to equipment to encourage behavior	
		a) Functioning school PA committee (i.e., school committee to meet once a school term).		
		b) All students participate in at least 120 minutes of timetabled PA per week (i.e., ensure PE and school sport are timetabled).		
		c) 50% of PE and school sport time devoted to MVPA (i.e., lessons designed to maximize huff and puff activity).		
		d) Annual reporting of students’ FMS and fitness (e.g. report cards describing student levels).		
		e) Promotion of active playgrounds (e.g. organized activities and access to equipment).		
		f) Involve family members in school-based PA (e.g. parents as helpers in PE and school sport).		
		*ii) Equipment and resources:* Each school will be provided with PA equipment (e.g. bats, balls etc.) and resources (e.g. activity cards) to support the implementation of the intervention based on their individual school needs (approx. $1,000).		
5) Community links	6 x visits	Community organizations (e.g. local football clubs) will be invited to the visit the study schools during PE/school sport. This will help to promote community sporting links.	▪Provide instruction	▪Social support
			▪Model or demonstrate the behavior	
			▪Provide information about opportunities in the local environment	

*Note:* FMS = Fundamental Movement Skills; PE = physical education; SCORES = Supporting Children’s Outcomes using Rewards, Exercise and Skills.

^1^Stage 2 teachers are the classroom teachers of students in the intervention schools.

**Table 2 T2:** SAAFE teaching principles and strategies

**Principles**	**Strategies**
**Supportive** – Lessons conducted in a supportive environment.	1. Publicly recognize all students’ effort, learning, achievements, and improvement.
	2. Provide feedback on student effort, process and progress (not results).
	3. Identify and manage inappropriate student behavior (e.g., teasing, over-competitiveness).
	4. Promote positive social interactions between students.
**Active** - Lessons involve a high level of movement and active learning time (ALT).	1. Use small-side games, circuits and tabloids to maximize participation.
	2. Ensure equipment is plentiful and developmentally appropriate.
	3. Monitor in-class physical activity using pedometers (i.e., approx. 75–85 steps/min of PE time is equal to 50% ALT).
	4. Use student leaders to set-up games and activities.
**Autonomous** – Lessons involve elements of choice and opportunities for graded tasks.	1. Ensure that tasks incorporate multiple challenge levels, and give students the freedom to select level of difficulty.
	2. Provide students with opportunities to create and modify rules and activities.
	3. Provide students with opportunities for leadership roles.
	4. Encourage students to assess their own skill performances (e.g., detect and correct their own errors).
**Fair** – Lessons provide all students with an opportunity to experience success.	1. Ensure tasks are not dominated by the most competent students.
	2. Modify the tasks to increase the opportunity for success (i.e., make the goals bigger, reduce the number of defensive players, alter the equipment used, revise the task rules).
	3. Ensure students are evenly matched in competitive activities.
	4. Acknowledge and reward participation and good sportsmanship.
**Enjoyable** – Lessons are designed to be enjoyable and engaging for all students.	1. Include a wide variety of games and activities.
	2. Provide engaging and age appropriate tasks.
	3. Avoid boring and repetitive activity (e.g., running around the field for a warm-up).
	4. Don’t use exercise or activity as punishment.

Parents will be engaged using the following strategies: a) newsletters describing intervention progress and encouraging PA and FMS practice, b) weekly FMS homework (using FMS activity cards to be completed by children at home under parental supervision), and c) a parent information evening focusing on parental strategies to promote PA and FMS development outside of school setting. Finally, students who have gained SCORES accreditation will be responsible for organizing recess and lunch-time physical activities for other students in the study schools.

*Organizational:* The research team will work with the schools to implement evidence-based policy and practice that is supportive of all students’ PA. The specific PA policies are provided in Table 1. A school committee will be established to guide a review of existing school policy and the implementation of new policies. The research team conducted an audit of each school’s equipment and resources. Intervention schools will be provided with PA equipment (e.g. bats, balls etc.) to support PA promotion, based on their individual requirements.

*Community:* The research team will conduct an audit of sport and PA organizations within each school’s local community. Community organizations will then be invited to visit schools during PE and school sport. The aim of this intervention component is to create partnerships between schools and community organizations. It will also serve to increase students’ awareness of, and participation in, extra-curricular sport and PA in their local community.

*Control group:* To prevent potential compensatory rivalry and resentful demoralization [54], the control schools will be provided with a condensed version of the program following the 12-month assessments. The condensed version of the program will include the professional learning workshops for teachers and students, strategies to engage parents and a review of school PA policy will be conducted. A PA equipment pack valued at approximately $1000 AUD (including pedometers, bats, balls, cones, goals etc.) will also be provided based on individual school requirements.

